### Sample size

The sample size was calculated [56] to obtain 80 % power to detect a 30 % difference between the two groups in the proportion of individuals with tobacco abstinence at 6 months (reference point = 30 % [36]). With a significant *P*-value of 0.05, these calculations showed that a total of 49 individuals per group was required, allowing for, with 15 % of patients potentially being lost to follow-up, a total of 120 needing to be included.

### Ethical principles and safety

The study is designed and conducted in accordance with the principles of the Declaration of Helsinki, seventh revision [57]. The patients are provided with both oral and written information regarding the study prior to obtaining their informed consent. The local ethics committee (CPP Sud Méditérannée V) approved this study, which is registered with the international standard randomized controlled trial number (NCT01570712).

## Discussion

The present study aims to assess the effectiveness of CBT coupled with VRET in the prevention of smoking relapse in subjects with smoking abstinence. VRET in association with CBT might represent an interesting alternative to CET. Several previous studies have supported the efficacy of VRET for smoking cessation [17–19]. VR environments can be used effectively in the treatment of nicotine addicts who wish to give up smoking [32]. We hypothesize that the findings of our study might be in agreement with their findings. From a theoretical perspective, CET appears to be a relevant method for complementing CBT according to the conditioning model [58]. It focuses on prompting the patient to contend with smoking-related stimuli (for example, the tobacco package, ashtrays, lighters, cigarettes) to mitigate smoking behavioural responses, to decrease withdrawal complications and to extinguish the craving. However, CET has an important limitation. Smoking-related stimuli are presented only in proximal confrontation patterns, such as images, photos and videos (that is, proximal risks), so there is no interaction with the environment or its multi-sensorial stimuli (distal risks), which are known to be of the utmost importance in smoking relapse. VRET might thus offer an alternative line of treatment by presenting the simultaneous presence of proximal and distal stimuli, compared to CET. Our hypothesis was that individuals would learn with VRET how to cope with proximal and distal risks and then use effective skills when facing similar environments *in vivo*.

The effects of VRET on health outcomes, such as anxiety, depression and quality of life, constitute an original aspect of our study, compared with previous studies. Several studies have reported that negative affect plays an important role in maintaining smoking dependence [21]. Our hypothesis was that VRET might have an indirect effect, mediated by the impact on smoking dependence, on negative affect (depression) and other psychological features, such as anxiety, self-esteem and quality of life.

The last objective is to demonstrate that this novel virtual environment is feasible and acceptable to the clinicians and patients who are potential program users. This objective is of the utmost importance, because the successful application of any technology as a tool to enhance evidence-based treatments is directly related to the ability of patients and clinicians to use the tool easily and effectively.

Several limitations must be borne in mind when considering our protocol. First, we chose to propose a widely used design for the CBT intervention, based on eight weekly individual therapeutic sessions of 60 minutes in duration. Because CBT is already a constraining treatment, we could not propose performing VRET in addition to CBT sessions of 60 minutes in duration. To keep the same number of sessions between the two groups, we proposed to the VRET treatment group two full sessions dedicated CBT (that is, concentrating the eight sessions of the CBT treatment group), followed by six sessions for VR exposure. This choice might mitigate the full integration of CBT and VRET and thus decrease the effectiveness of their associations. The differences in group conditions will be examined with greater attention when interpreting the results of this study. In addition, this choice might also decrease the effectiveness of CBT in the group with VRET because the principles cannot be learned as rapidly (that is, in two sessions) by patients. However, the therapist can help the participants during the VRET sessions to review the principles of CBT once they are immersed in the virtual environments. Second, the virtual environments used in our trial are situations featuring only pleasant connotations (such as being in a restaurant or on the beach). A whole gamut of cues with negative connotations (such as job stress, arguing with one’s spouse, acute stress, receiving bad news) that can trigger tobacco cravings exists as well in reality. In fact, former smokers might be more sensitive to cues with negative emotional valences and more prone to relapse in this context, rather than during positive events. Future studies focusing on situations with negative connotations should be performed. Finally, heart rate (HR) was examined only in the CBT coupled with VRET treatment group and not in the CBT treatment group alone. Because the CBT treatment group did not include cue exposure therapy, we did not include a measurement of HR data. Indeed, HR could be considered physiological reactivity to smoking-related cues, and it was measured during the cue presentations (VRET session). Our hypothesis was that VRET lowers physiological reactivity to smoking-related cues and that we would observe a significant decrease in HR during the VRET sessions. We expect to observe a negative correlation between HR and the number of VR sessions. The absence of comparisons for this parameter between the two groups is a limitation of our study. However, HR is one of the main correlates of craving, and we compared smoking cravings between the two groups with the French Tobacco Craving Questionnaire (FTCQ-12).

Finally, the findings of our study might have significant implications for future population-based interventions. Because VRET is now available at a low cost and is simple to use [19], this interactive therapeutic method might be easily implemented in clinical practice if our study confirms its efficacy. We can also hypothesize that, in the long run, patients will practice VR exposure at home. Advances in computer science, hardware performance and equipment availability make this assumption entirely probable. Events such as the acquisition of the Oculus company, which assembles affordable VR equipment, by Facebook or the use of ordinary Samsung cell phones as screens for HMD Gear VR could represent premises for the generalization of VRET in the general population and could induce a major shift in the media paradigm in post-modern societies.

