### Treatment groups

The protocol includes eight weekly individual therapeutic sessions of 60 minutes in duration for both groups. The eight sessions are conducted by psychologists with training in cognitive behavioural approaches and virtual reality exposure. The content of the CBT is similar in the two groups but delivered differently between the two groups.CBT treatment groupThe subjects receive eight weekly individual sessions of CBT. The CBT was developed by three psychologists (CG, NP and [name]) with training in the assessment and treatment of health problems and specific training in CBT. The content was first developed independently by two of the psychologists (CG and NP), based on international guidelines, the scientific literature on smoking cessation and relapse and their professional experience [4, 7, 26, 27]. The sessions pivoted on all of the key principles of CBT. It was collaborative, present-oriented, and problem-focused. Any discrepancies were resolved by consensus with a third psychologist ([name]). The CBT was then tested on a small sample of patients (n = 10), confirming its acceptability and validity. The sessions were designed to target the factors linked to smoking relapse after smoking cessation, including: 1) definition of relapse and identification of causes leading to relapse; 2) analysis and detection of high risk situations; 3) explanation of automatic thoughts and beliefs leading to tobacco consumption; 4) presentation of strategies (for example, behavioural coping strategies and cognitive coping strategies); 5) management of negative emotions; 6) management of assertiveness. The sessions are described in Additional file 1.CBT coupled with VRET treatment groupThe subjects receive two weekly individual sessions of CBT, followed by six weekly individual sessions of VRET. VRET consists of exposing the patient to situations considered to incur high risk of tobacco relapse and aimed at the reduction of cue reactivity by extinction. The therapist can help the subject to review the CBT principles and strategies during the VR exposure, using various complex environments tailored to the project (detailed below). The VR exposure is context graded because the smoking cues can vary in intensity (for example, number of avatars smoking around the patient, presence of cigarette boxes spread on tables). Given individual differences in the relevance of craving-specific stress among participants and to determine the order of exposure to virtual situations, a hierarchy of virtual environments (VEs), from the least craving and anxiety induced to the most craving and anxiety induced, was established for each participant independently. Throughout the exposure to VEs, the participants were invited to progress to the next VE when they had reached a comfortable level of emotion or craving in the current environment. Consequently, if required, exposure to a particular event or situation could be repeated. The therapist could monitor the subject's reactions according to the displayed situation. The session occurring in VEs lasts approximately 50 to 60 minutes. This duration is standard and does not depend directly on extinction or craving reduction. However the 10-minute lapse allows the therapist to ensure that the end of exposure take place when arousal or craving is lowered, thus avoiding any accidental sensitization phenomenon. Besides, when extinction and craving reduction do take place before minute 50, participants are invited to proceed to the next context graded VE [28, 29].

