
The following data are collected at each session (see Table 2).

**Table 2 Tab2:** Assessment during the eight therapy sessions

	Cravings at the beginning of the session	Cravings during the session	Cravings at the end of the session	HR^1^	HRV^2^	PQ^3^	SSQ^4^
CBT	X		X				
CBT coupled with VRET	X	X	X	X	X	X	X

^1^Heart rate; ^2^heart rate variability; ^3^Presence questionnaire; ^4^Simulation Sickness Questionnaire

HR and HRV are measured during the VRET session

PQ and SSQ are measured at the end of the VRET session

Perception of presence is assessed by the Presence Questionnaire (PQ), version 3.0 [50]. The PQ consists of 32 items rated on a 7-point scale, and factor analyses found 6 factors: involvement, interface quality, adaptation and immersion, consistency with expectation, visual fidelity and auditory fidelity [51]. The PQ is a self-report instrument that has been validated in many empirical studies [50–53] and has also demonstrated a relationship between presence and anxiety [52]. A high score indicates a satisfactory perception of presence.Symptoms reported to be associated with simulator sickness are assessed with the Simulation Sickness Questionnaire (SSQ) [53]. The SSQ is a 16-item self-report instrument with scores ranging from 16 (absence of cybersickness) to 48 (high cybersickness). Factor analyses found three main factors: oculomotor (for example, blurred vision), disorientation (for example, dizziness) and nausea (for example, vomiting).*Heart rate* (HR) and *heart rate variability* (HRV) are evaluated with a heart rate monitor (apparatus for technical description) for the duration of each therapeutic session. The HR reflects the average heart rate recorded during the therapeutic session. The HRV indicates the fluctuations in heart rate around an average heart rate [30]. HR and HRV reflect the autonomic responses involved in emotional arousal, most notably during anxiety, during which the HR is expected to increase and the HRV to decrease [54]. There is evidence that heart rate changes are correlated with presence [55]. Furthermore, HR is one of the main correlates of craving [8]. HR and HRV represent alternative objective measurements of anxiety response, presence and craving.

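### The expected fall in heart rate over VR sessions cannot by itself show reduced cue reactivity, because cue strength tends to rise with session number and heart rate is a raw session mean in one arm

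*Protocol article*

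**What the plan says.** All places are in the protocol article.

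- **Hypothesis and expected evidence** (Discussion, limitations): "Our hypothesis was that VRET lowers physiological reactivity to smoking-related cues", followed by "We expect to observe a negative correlation between HR and the number of VR sessions".
- **Order of exposure** (Treatment groups): each participant has "a hierarchy of virtual environments (VEs), from the least craving and anxiety induced to the most craving and anxiety induced".
- **Pace** (Treatment groups): "the participants were invited to progress to the next VE when they had reached a comfortable level of emotion or craving", and "Consequently, if required, exposure to a particular event or situation could be repeated". A participant whose craving settles early may also move on within the same session.
- **Operator control** (Software and virtual environments): the experimenter can trigger events that strengthen induced craving.
- **Measure** (Evaluation outcome): "The HR reflects the average heart rate recorded during the therapeutic session". The note to Table 2 adds: "HR and HRV are measured during the VRET session".
- **Meaning** (Evaluation outcome): "HR and HRV represent alternative objective measurements of anxiety response, presence and craving".
- **Admitted limitation** (Discussion): heart rate has no between-group comparison. Graded exposure is not mentioned as a complication.

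**The concern.** Reactivity is a response to a cue of given strength, measured against some reference. The expected evidence is a trend in a level, over sessions in which cue strength is meant to climb. Extinction pushes heart rate down and stronger cues push it up, so session number carries both. Because progression depends on how quickly a participant becomes comfortable, those who extinguish fastest may meet the strongest cues soonest. The distortion then differs between participants and is tied to the effect of interest.

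A fall is ambiguous too. Familiarity with the headset and the setting, or weaker presence, would lower a session mean without any change in the response to smoking cues, and no control series exists to remove such time effects.

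At stake is the mechanistic reading: a flat or rising trend could be taken as absence of extinction, and a falling one as proof of it, when neither follows.

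**Working it through.** **The plan's own figures.** None is given for heart rate. The only computed design figure is 49 per group for abstinence. It reproduces (two-sided 0.05, 80 % power, 30 % against 60 %: 42 per group without continuity correction, 49 with it) and plays no part here.

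**What the session slope identifies.** For participant *i* in VR session *s* (1 to 6), write

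HR = aᵢ + b·Rᵢₛ − e·(s − 1) − h·(s − 1) + error,

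where R is the hierarchy rank, b the rise in heart rate per rank, e the extinction per session and h the general habituation per session. If rank rises by an average of ρᵢ per session, then

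slope on session = b·ρᵢ − e − h.

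Only this sum is estimable from session number and heart rate. The pace ρᵢ varies between participants because exposures may be repeated and several environments may fall in one session.

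**Effect of the pace (assumed b = 2, e = 1, h = 0 bpm).**

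- ρ = 0: 2 × 0 − 1 = −1
- ρ = 0.5: 2 × 0.5 − 1 = 0
- ρ = 1: 2 × 1 − 1 = +1

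The same true extinction shows as a fall, as nothing or as a rise.

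**Simulation, all heart-rate values assumed.** 51 participants (60 × 0.85), 6 sessions, between-participant SD 10 bpm, within-participant SD 5 bpm, two-sided 5 % test on the mean within-participant slope, 2,000 runs. Grading is the product b·ρ.

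| Extinction | Grading | Habituation | Net slope | Mean r | Significant fall | Significant rise |
|---|---|---|---|---|---|---|
| 0 | 0 | 0 | 0 | 0.00 | 2.45 % | 2.55 % |
| 1 | 0 | 0 | −1 | −0.15 | 100 % | 0 % |
| 1 | 1 | 0 | 0 | 0.00 | 2.0 % | 2.8 % |
| 1 | 2 | 0 | +1 | +0.15 | 0 % | 100 % |
| 0 | 0 | 1 | −1 | −0.15 | 100 % | 0 % |
| 0 | 1 | 2 | −1 | −0.15 | 100 % | 0 % |

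Hand check: the standard error of the mean slope is 5/√17.5/√51 = 0.167, so a net slope of 1 lies about 6 standard errors from zero. The problem is therefore not lack of power. Row 3 contains real extinction and looks like row 1. Rows 5 and 6 contain none and look like row 2.

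**Can the article's other data separate the terms?** The Presence Questionnaire is completed at the end of VRET sessions, so lower presence can be examined. A cue-free reference cannot be assumed from the two opening CBT sessions of the VRET arm: Evaluation outcome speaks of recording throughout each therapeutic session, but the note to Table 2 and the Discussion tie heart rate to the VRET sessions.

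**The case against.** The strongest reply is that this is one sentence of expectation in a limitations paragraph. Heart rate is not among the stated objectives, and the Statistical analysis section specifies no heart-rate model. That stands and limits the weight of the point. But the sentence fixes a direction and ties it to a hypothesis, so the reading it invites can be judged.

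Other replies hold against stronger readings that a reader might infer:

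- **That no resting reference is recorded.** The article is condensed, and the monitor may run before exposure begins. The text supports only that the reported measure is a session average.
- **That this is the sole evidence on mechanism.** Craving is rated before, during and after VRET sessions, the FTCQ-12 is taken at T0 to T4, and the Discussion also expects heart rate to fall during VRET sessions, which may mean within a session.
- **That session number and cue strength are locked together.** Repeats, several environments per session and the comfort rule loosen the link and may restrain the rise in the session mean.
- **That grading creates a spurious fall.** It pushes heart rate up, so alone it can only mask or reverse. The ambiguity of a fall comes from the raw level, the single arm and the non-specific meaning of heart rate.
- **That the number of sessions is a per-participant count that hardly varies.** Session order is the natural meaning.

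The admitted lack of a between-group comparison covers part of the habituation problem. It does not cover grading, which a control arm without cue exposure would not remove.

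**Conclusion.** The point holds as a caution on an ancillary mechanistic measure. Following the article as written, neither the sign nor the significance of the correlation between heart rate and session number identifies reduced reactivity to smoking cues. A null or positive trend may conceal extinction, and a negative one may reflect general habituation or lower presence.

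The size in this trial is unknown. The bpm slopes, SDs and linear form are assumptions that show how the terms cancel or imitate one another; they are not estimates. The conclusion needs only that cue strength tends to rise over sessions, as the hierarchy intends, and that stronger cues raise heart rate, as the article's own account of heart rate implies. The abstinence outcome, its sample size and the between-group comparisons are untouched.

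**What to change.** 1. Log the environment and its rank in the participant's hierarchy for each exposure.
2. Replace the simple correlation with a mixed model with participant random effects, separate terms for session and rank, and the Presence Questionnaire score already collected.
3. Rest any extinction reading on repeat exposures to the same environment and on change within an exposure. Rank depends on earlier responses, so adjustment alone is not enough, and the session term still contains general habituation.
4. Where recordings contain a pre-exposure segment, express heart rate as change from it.
5. If session and rank cannot be separated, report the trend as descriptive and make no claim of reduced cue reactivity from it. Add graded exposure to the stated limitations.

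The cost is one log field and a different model, with no change to treatment. Recruitment began in August 2014, so rank or rest data not recorded for completed sessions cannot be recovered. Repeat exposures happen only where needed, so those analyses will rest on a selected and possibly small subset.

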### Trial status

The study started including participants in August 2014, and the recruitment is ongoing.

## Abbreviations

BDI: Beck Depression Inventory
CBT: cognitive behavioural therapy
CDS-12: Cigarette Dependence Scale
CET: cue exposure therapy
DSM-V: Diagnostic and Statistical Manual of Mental Disorders, 5th version
EULA: end user license agreement
FTCQ-12: French Tobacco Craving Questionnaire
GLE: game level editor
HR: heart rate
HRV: heart rate variability
PQ: Presence Questionnaire
SF-12: Short Form Health Survey
SSQ: Simulation Sickness Questionnaire
STAI: State-Trait Anxiety Inventory
VE: virtual environment
VR: virtual reality
VRET: virtual reality exposure therapy
